### 2.4. Study Size

The DUTCH CCS registry is a prospective, observational, single-arm study designed for descriptive and exploratory analysis. The study aims to enroll 1000 patients with chronic coronary syndrome (CCS), treated with low-dose rivaroxaban in addition to aspirin. The target sample size reflects a balance between feasibility and the goal of generating clinically meaningful insights within the study’s timeframe. Enrollment will continue beyond 1000 patients if needed to compensate for a dropout rate exceeding 5%, ensuring that sufficient patients are available for 12-month follow-up.

Although no formal power calculation was performed, the sample size is expected to provide adequate precision to estimate event rates for major outcomes, including MACEs and major bleeding, with 95% confidence intervals. Expected event rates were informed by incidence proportions observed in the COMPASS trial. However, due to the shorter follow-up period in our study (12 months vs. 23 months in COMPASS), the incidence of similar endpoints is expected to be lower. Conversely, the broader definition of clinical outcomes in our registry—which includes not only conventional MACEs but also clinically indicated coronary, peripheral, or carotid revascularization and stent thrombosis—may lead to higher overall event rates.

Furthermore, although the patient population largely resembles that of COMPASS, we include patients with higher CHA_2_DS_2_-VASc scores, potentially increasing the observed number of ischemic events. Based on these factors, we estimate that most clinical endpoints will occur in 1% to 5% of patients, which allows for reasonably precise estimates of outcome frequencies in relevant subgroups.

To support interpretation and assess the robustness of our findings, we will conduct sensitivity analyses. These include stratified analyses by clinical risk factors (such as diabetes, PAD, or prior MI), comparisons based on narrow versus broader endpoint definitions, evaluation of patients with complete versus incomplete follow-up, and exploration of site-level variability. These analyses will contextualize the observed outcomes and help determine the consistency of results across different analytical assumptions, despite the absence of formal hypothesis testing.

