### 2.8. Data Analysis

All statistical analyses were performed using IBM SPSS Statistics, version 28.0 (IBM Corp., Armonk, NY, USA).

The statistical analyses are explorative and descriptive. All analyses are performed for the total study population (overall analyses). The study period for analyses is defined as the time from the start of rivaroxaban until the end of the 1-year follow-up.

Descriptive statistics are performed for both primary and secondary study parameters. Continuous variables are expressed as mean ± standard deviation and as medians with minimum, maximum, 25th, and 75th percentiles. Categorical variables are presented by frequency tables (absolute and relative frequencies). Incidence proportions are computed together with corresponding exact 95% confidence intervals (CIs) for primary and secondary endpoints. Cumulative incidence of events or survival probabilities and 95% confidence intervals are estimated using Kaplan–Meier estimates for primary and secondary endpoints. The follow-up starts per definition on the date of the start of treatment and ends at the date of a first event, date of loss to follow-up, or date of end of the one-year study period, whichever comes first. The incidence of events over time is studied with the use of Kaplan–Meier methods. Patients who do not experience an event of interest by the end of their individual observation period are censored.

To control for confounding, the primary analyses will employ multivariable Cox proportional hazards regression models, with adjustment for prespecified baseline covariates known to influence clinical outcomes: age, sex, presence of diabetes mellitus, renal function, and CHA_2_DS_2_-VASc score. Model assumptions, including proportional hazards, will be assessed using Schoenfeld residuals. In addition, propensity score methods will be implemented as sensitivity analyses to further address confounding and potential selection bias. Propensity scores will be estimated using logistic regression models including the aforementioned covariates. These scores will be incorporated via adjustment for the propensity score as a covariate in the Cox model.

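### The primary Cox model adjusts for CHA2DS2-VASc alongside age, sex and diabetes, which the score already counts, and five terms are too many for the rarest endpoints

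*Protocol article*

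**What the plan says.** Section 2.8 (Data Analysis) states that, to control for confounding, the primary analyses use multivariable Cox models with "adjustment for prespecified baseline covariates known to influence clinical outcomes: age, sex, presence of diabetes mellitus, renal function, and CHA_2_DS_2_-VASc score". The same covariates feed a propensity score, to be entered as a covariate in a Cox model as a sensitivity analysis. The section does not say how the covariates are coded and gives no smaller set for rarer endpoints. It also describes the analyses as explorative and descriptive, and it plans exact confidence intervals for incidence proportions and Kaplan–Meier estimates for all primary and secondary endpoints.

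Section 2.4 (Study Size) sets a target of 1000 patients and says "Although no formal power calculation was performed". On frequency it says "we estimate that most clinical endpoints will occur in 1% to 5% of patients". It adds that the broader outcome definition, with revascularization and stent thrombosis, "may lead to higher overall event rates". It also plans stratified results by risk factors such as diabetes, PAD and earlier MI.

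Sections 2.1 and 2.4 describe a single-arm study in which every patient receives rivaroxaban plus aspirin.

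**The concern.** CHA2DS2-VASc is a sum. If it contains age bands, female sex and diabetes, then a model with the score and those same variables asks what diabetes does while the total score stays fixed. For a patient with diabetes to have the same total as one without, some other score item must be lower. That is not the question a reader has in mind when looking at an adjusted hazard ratio for diabetes.

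In most studies this would be harmless, because overlap among pure adjustment variables does not disturb the estimate for a separate exposure. Here there is no separate exposure. The covariate hazard ratios are what the primary regression will deliver, so the overlap falls directly on the reported numbers. The likely misreading is that diabetes and sex matter less on this treatment than they do.

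The second issue is the number of events. Five terms are a lot for an endpoint that occurs in about 1% of 1000 patients, and this list applies to rare and common endpoints alike.

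**Working it through.** **Inputs from the protocol article.** 1000 patients (Section 2.4); 1% to 5% for most endpoints (Section 2.4); five covariates, "age, sex, presence of diabetes mellitus, renal function, and CHA_2_DS_2_-VASc score" (Section 2.8), counted as one term each because coding is not given; major bleeding of 3.1% on the combination in COMPASS (Section 1) over 23 months (Section 2.4). The article gives no event count or power figure, so there is nothing to reproduce.

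**Is the score really overlapping?** The article does not list the score's items, so its usual make-up is assumed: age bands, female sex, diabetes, hypertension, heart failure, prior stroke, vascular disease. The entry thresholds in Table 1 (above 3 for men, above 4 for women) fit with female sex adding one point. On this definition three of the other four covariates are inside the score; renal function is not.

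**What the coefficient means.** Let b be the coefficient of diabetes and g that of the score. Having diabetes adds one point, so its effect with the other items held fixed is b + g, while the table of results shows b alone. If higher scores carry higher risk (g > 0), the printed hazard ratio is too small by a factor exp(g). The same holds for sex. Age is only partly tied to the score, through its bands.

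**Size, by simulation.** None of these settings comes from the article: N = 1000, one year, 400 runs per setting, age 68 (SD 9), 22% women, 45% diabetes, hypertension 50–95%, heart failure 5–30%, stroke 1–10%, and assumed effect sizes.

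- Diabetes at about 50 events: median log-HR 0.38 with the score, 0.58 without; exp(0.38) = 1.46 and exp(0.58) = 1.79.
- Sex at about 50 events: 0.03 with, 0.21 without; exp(0.03) = 1.03 and exp(0.21) = 1.23.
- The gaps, 0.58 − 0.38 = 0.20 and 0.21 − 0.03 = 0.18, are nearly equal, as the b + g argument predicts.
- Variance inflation of the score: 2.3 in the base scenario, 1.9 to 3.4 in moderate ones, 4.5 in an extreme one. Dropping the score lowers the factors for age from 1.85 to 1.2, diabetes from 1.36 to 1.0 and sex from 1.25 to 1.0.
- Median SE for diabetes at about 50 events: 0.335 with, 0.294 without. The ratio of upper to lower 95% limit is exp(2 × 1.96 × SE), which gives 3.7 and 3.2.

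A second simulation (300 runs; 25% women, 45% diabetes, 20% heart failure, 70% hypertension, 6% stroke, age 69 ± 9; assumed effects) gave a diabetes coefficient of the wrong sign in 25% of runs with the score and 6% without, at 50 events. Part of that difference is the smaller target value, not only the loss of precision.

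**Events per covariate** = 1000 × rate / 5.

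| Rate | Events | Per covariate |
|---|---|---|
| 1% | 10 | 2 |
| 2% | 20 | 4 |
| 3% | 30 | 6 |
| 5% | 50 | 10 |
| 8% (assumed, composite) | 80 | 16 |

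With 5% dropout (N = 950) the 1% and 5% rows become 9.5 and 47.5 events, or 1.9 and 9.5 per covariate.

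**Major bleeding.** Linear proration gives 3.1% × 12/23 = 1.6%, about 16 events, and 16/5 = 3.2 per covariate. If all of the 3.1% fell in the first year, the count would be 31, or 6.2 per covariate.

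**Does sparsity break the fit?** With five terms in the first simulation, separation or exploding coefficients occurred in about 11% of fits at about 10 events (about 4% in the second) and in none at about 30 or 50. At about 30 events the diabetes limits still differed by a factor of 5.6.

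**The case against.** The strongest reply has four parts.

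First, the model is valid as a joint adjustment. The score also carries hypertension, heart failure and stroke, so it is not a linear combination of the other terms, and the collinearity is moderate. For sex and diabetes the usual effect can be recovered as b + g. The signal from the remaining items is not hidden either; with age, sex and diabetes in the model, the score's own coefficient carries most of it. All of this stands. The component hazard ratios are therefore hard to read, and a reader who infers that they are uninterpretable or cannot be estimated goes further than the evidence.

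Second, a reader might infer that every model is unstable because only 10 to 50 events are expected. The article does not support that. Its range covers most endpoints, not all, and Section 2.4 says the broad composite may run higher. At 50 events there are already 10 per covariate, and no separation appeared at 30 or 50.

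Third, these models are not the only planned source of statements about who has events. Section 2.4 plans stratified results, and Section 2.8 plans incidence and Kaplan–Meier estimates. That stands and limits the damage.

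Fourth, the analyses are called explorative, and an article may leave coding and penalisation to an analysis plan. That is fair for those details. It does not cover the covariate list, which is stated outright for a model the same section calls primary.

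Prorating the bleeding rate is also open to challenge: Section 4 says bleeding tends to appear in the first months, so 16 events may be too low.

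**Conclusion.** The point holds in a limited form. The primary Cox model double-counts age, sex and diabetes through the score. Because a single-arm study offers no exposure contrast, this changes the only hazard ratios the model yields. For sex and diabetes the printed ratios are effects at a fixed total score. They are attenuated when the score is positively related to risk, and somewhat less precise. The illustrated size for diabetes, 1.46 against 1.79, rests on assumed prevalences, assumed effects and the score's usual definition; the change of meaning rests on the definition alone and does not go away with more events.

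Sparsity is a separate and narrower fault. It concerns the rarest endpoints, at 2 to about 6 events per covariate. Major bleeding falls in this zone at 3.2 per covariate under linear proration and 6.2 if all the COMPASS bleeding fell in the first year. It does not concern the composite if that reaches 50 or more events.

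The incidence proportions and Kaplan–Meier curves, which answer the registry's descriptive aim, are untouched. The plan should be changed, but the registry's main results do not depend on it.

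**What to change.** 1. Use one representation per model. Either fit the components (age, sex, diabetes, renal function, with heart failure, hypertension and prior stroke added where events allow), or fit the score plus renal function as a separate model. Do not put the score and its components in the same model, and state the coding.
2. State that the hazard ratios are descriptive prognostic associations among treated patients, not treatment effects adjusted for confounding. The missing exposure contrast also affects the propensity-score analysis; changing the covariate list does not cure that.
3. For endpoints with few events, use a reduced or penalised model (for example Firth's), or report incidence with its exact interval and no regression.

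Step 1 does not replace step 3. Four component terms give 10/4 = 2.5 events per covariate at 10 events and 50/4 = 12.5 at 50, and separation at about 10 events only falls from about 11% to about 10% of fits. The two-term score model does better, at 10/2 = 5 and 50/2 = 25.

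The cost is two short models instead of one, and possibly software other than the named SPSS version for a penalised fit. No new data are needed. As Section 2.1 says the article was written after data collection, the change should be dated and declared.

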The VOYAGER-PAD trial produced similar findings. In patients with PAD who underwent revascularization, rivaroxaban combined with aspirin reduced MACEs more effectively than aspirin alone [13].

Based on this evidence, the European Society of Cardiology guidelines recommend low-dose rivaroxaban for CCS patients who have completed twelve months of dual antiplatelet therapy (DAPT) without major bleeding and have no history of stroke or transient ischemic attack. This recommendation holds a Class IIa–IIb, Level A rating [14,15]. Clinicians should especially consider this strategy for patients with high thrombotic risk and acceptable bleeding risk. They may also apply it to patients with moderate thrombotic risk.

Although clinical trials have shown promising results, researchers still lack sufficient real-world data on low-dose rivaroxaban in high-risk CCS patients. To address this gap, the DUTCH CCS registry has been established. Moreover, randomized trials often exclude elderly, frail, or multi-morbid patients. This results in a paucity of real-world evidence on DPI’s net clinical benefit across broader populations. Our registry addresses this gap by evaluating DPI in a pragmatic clinical environment, with broader inclusion criteria reflective of contemporary cardiology practice.

This observational study focuses on Dutch patients with CCS who face a high risk of ischemic events but have a relatively low bleeding risk. The study evaluates the safety and effectiveness of DPI in routine clinical settings. We hypothesize that DPI improves clinical outcomes without significantly increasing bleeding, even under real-world conditions. Because the study includes a broader high-risk population and defines outcomes more broadly—including revascularization and stent thrombosis in addition to MACEs—we expect to observe a higher rate of ischemic events than reported in randomized trials.

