## 2. Methods

### 2.1. Study Design

The DUTCH CCS registry is a nationwide, multicenter, prospective, observational, single-arm study involving 1000 CCS patients who are treated with rivaroxaban 2.5 mg twice daily in addition to aspirin 80–100 mg once daily. The study is conducted in twelve interventional cardiac centers, situated across various regions of The Netherlands. Investigators at Isala Hospital in Zwolle are responsible for the oversight and coordination of the registry and data management. Figure 1 presents the geographic locations and specific roles of the twelve participating study sites.

From December 2020 to May 2022, this registry has been enrolling consecutive adult patients (aged 18 years or older) who are diagnosed with CAD, exhibiting one or more of the following high-ischemic-risk features: (1) coexistence of PAD, (2) recurrent MI (subsequent to an initial MI), (3) diabetes mellitus, (4) chronic kidney disease (eGFR 30–59 mL/min/1.73 m^3^), (5) heart failure (with an ejection fraction ranging from ≥30% to 50%) and New York Heart Association (NYHA) class I or II, and/or (6) CHA_2_DS_2_-VASc score (greater than 3 for men or greater than 4 for women). Although patient recruitment was completed between December 2020 and May 2022, the study is designed as a prospective observational registry from the outset.

All data collection and follow-up procedures are conducted in real time, in accordance with a predefined protocol established prior to enrollment. While the current manuscript is written after data collection, the analysis is based on prospectively gathered data, consistent with the study’s original design and intention.

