**Inclusion Criteria**
Adult patient (≥18 years) Diagnosis of CAD and high risk of ischemic events Patients at high risk of ischemic events include, amongst others, the following: ○ CAD + PAD ○ CAD + recurrent myocardial infarction (previous myocardial infarction followed by a second) ○ CAD + diabetes mellitus (all types) ○ CAD + chronic kidney disease (eGFR 30–59 mL/min/1.73 m^2^) ○ CAD + heart failure (ejection fraction ≥ 30–50%) and NYHA class I or II ○ CAD + high CHA_2_DS_2_-VASc score (men > 3 or women > 4) Patients can only be enrolled in the study if the decision to treat with rivaroxaban plus aspirin has been made by the treating physician in advance and independent of study inclusion within 4 weeks prior to study inclusion. Patients who are willing to participate in this study (signed informed consent)

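### Section 2.8 gives the primary label to confounder-adjusted Cox models and adds a propensity score, but the registry has one arm and defines no exposure contrast. The one-year incidence estimates already planned should be primary.

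*Protocol article*

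**What the plan says.** **Design.** Section 2.1 describes a "nationwide, multicenter, prospective, observational, single-arm study involving 1000 CCS patients who are treated with rivaroxaban 2.5 mg twice daily", together with aspirin. Table 1 adds: "Patients can only be enrolled in the study if the decision to treat with rivaroxaban plus aspirin has been made by the treating physician". Section 2.1 and Table 1 therefore put every patient on DPI at entry. Section 4 (Discussion) lists the lack of a control group as a limitation. It mentions historical controls or propensity-score matching only as possible later work, because suitable external data did not exist when the study began.

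**Analysis.** Section 2.8 first calls the analyses exploratory and descriptive and applies them to the whole cohort. It plans incidence proportions with exact 95% confidence intervals, and Kaplan–Meier estimates with 95% confidence intervals, for the primary and secondary endpoints. It then changes direction: "To control for confounding, the primary analyses will employ multivariable Cox proportional hazards regression models". The covariates are age, sex, diabetes, renal function and CHA2DS2-VASc score. It goes on to say that "propensity score methods will be implemented as sensitivity analyses to further address confounding and potential selection bias", and specifies: "Propensity scores will be estimated using logistic regression models including the aforementioned covariates". The score enters the Cox model as a covariate.

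**Hypothesis.** The Introduction says: "We hypothesize that DPI improves clinical outcomes without significantly increasing bleeding, even under real-world conditions". Section 2.4 describes its sensitivity analyses as helping to judge consistency "despite the absence of formal hypothesis testing".

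**The concern.** Confounding belongs to a contrast between exposed and unexposed patients, and a propensity score is the probability of being on one side of that contrast. A cohort in which everyone starts DPI has no such contrast, and Section 2.8 does not define another. The model labelled primary therefore does not target the quantity that Section 2.5 sets as the primary endpoint, which is the occurrence of the composite, or of major bleeding, within one year.

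Two things are at stake. Reporting adjusted or propensity-adjusted results from this cohort would suggest that confounding of a treatment effect had been handled, although no treatment effect was estimated. And an undefined exposure, in an article that Section 2.1 says was written after data collection, leaves room to choose the contrast once the data are known.

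**Working it through.** The article gives no power, effect size or derived sample size for a comparison, so there is no figure to reproduce. The check is structural.

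**Inputs.** n = 1000 in one arm (Section 2.1); exposed share at entry 1.0 (Section 2.1, Table 1); five covariates (Section 2.8); expected rates for most endpoints 1% to 5% (Section 2.4), which is 10 to 50 events in 1000.

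**1. Information on a DPI effect in the Cox model.** The information on a log hazard ratio for a binary exposure is approximately d × a × (1 − a), with d events and exposed share a. At the upper expected rate this is 50 × 1 × (1 − 1) = 0. No number of events changes that. The model can still be fitted to the five covariates, but every coefficient then describes a prognostic factor.

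**2. Propensity model, if the outcome is receipt of DPI.** With every outcome equal to 1, the log-likelihood is −Σ log(1 + exp(−ηᵢ)), where ηᵢ is the linear predictor of patient i. It rises towards 0 as the intercept grows and never reaches a maximum. A trial fit used 1000 simulated patients; the covariate values are an assumption, but the result does not depend on them. No fit converged:

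| Iterations allowed | Intercept | Fitted score (lowest = highest) |
|---|---|---|
| 5 | 6.2 | 0.99797 |
| 10 | 11.2 | 0.99999 |
| 20 | 21.3 | 1.00000 |
| 30 | 26.5 | 1.00000 |

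**3. Using that score in the Cox model.** A constant score c with coefficient γ contributes exp(γc) to the numerator and to every term of the denominator of the partial likelihood. It cancels, so γ cannot be estimated and nothing is adjusted. Nor can the score address selection into DPI, because the article describes no dataset of patients who were not prescribed it.

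**4. What a single arm does support.** Exact (Clopper–Pearson) limits for x events in n are the 2.5% point of Beta(x, n − x + 1) and the 97.5% point of Beta(x + 1, n − x):

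| Events / n | Rate | 95% CI |
|---|---|---|
| 10 / 1000 | 1.0% | 0.48% to 1.83% |
| 50 / 1000 | 5.0% | 3.73% to 6.54% |

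These need neither confounder adjustment nor a propensity score, and Section 2.8 already plans them.

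**5. Other contrasts inside the cohort.** Section 2.4 names strata (diabetes, PAD, prior MI), complete versus incomplete follow-up, and sites. Section 2.6 records discontinuation. Section 2.8 ties neither the Cox model nor the propensity score to any of these, and its statement that all analyses use the total population points away from them. Diabetes is already an adjustment covariate. PAD and prior MI are not among the five, so a model for either could be fitted if the plan said so.

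**The case against.** **Incidence is already planned.** A reader might infer that the primary endpoints will not be estimated at all. The article does not support that: exact proportions and Kaplan–Meier estimates for the primary endpoints come before the Cox model in Section 2.8. This stands, and it narrows the point to which analysis is called primary.

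**The propensity outcome is unstated.** A reader might infer that the propensity model certainly cannot be fitted. The non-convergence above holds only if the outcome is receipt of DPI. Section 2.8 does not say so, and an analysis plan that is not shown might define a within-cohort exposure. This stands as a condition. It does not rescue the text, which fixes the covariates, the estimation model and the use of the score without giving it a contrast.

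**Redundancy of the score.** It is also tempting to say that, even with a comparator, a score built from the same five covariates would add nothing. That has not been shown. The fitted score is a nonlinear function of the covariates, and the question does not arise in a single arm.

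**The article disclaims causality.** The Abstract says the registry is not designed to establish causality, and Section 4 admits the lack of a control group. These statements reduce the risk of misleading readers. They also sharpen the conflict with a primary analysis whose stated purpose is to control confounding. The Introduction's hypothesis is a lesser matter, since no test is attached to it.

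**Conclusion.** The point holds in this form: the primary label is on an analysis with the wrong target, and the propensity analysis cannot be run as described. Both conflict with the single-arm design, with the descriptive aim stated in Section 2.8, and with Section 4, which leaves propensity matching and historical controls to possible later work. This is a method the article states, not a detail left to an analysis plan.

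The size is structural: exposed share 100%, unexposed 0%, and zero information on a DPI effect. The sample size, endpoint definitions, data items and planned incidence estimates are unaffected. The conclusion on the Cox model rests on no exposure term being defined. The conclusion that the propensity model has no finite solution rests on the further assumption that its outcome is receipt of DPI.

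**What to change.** 1. In Section 2.8, make one of the planned one-year estimates the primary analysis of each primary endpoint, and say which. Kaplan–Meier cumulative incidence uses patients with incomplete follow-up; the exact proportion can be supportive.
2. Relabel the Cox model as an exploratory prognostic-factor analysis and remove the stated purpose of controlling confounding.
3. Delete the propensity score from the current plan unless an explicit within-cohort exposure and comparison group is defined. Otherwise keep it for the possible external-control work in Section 4.
4. Reword the Introduction's hypothesis as an estimation objective: the one-year incidence of the composite and of ISTH major bleeding in CCS patients treated with DPI. This agrees with Section 2.4.

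**Cost.** No new data or patients are needed. The change is still more than editorial: Section 2.1 says the manuscript was written after data collection, so a change in what is called primary should be dated and declared as made at that stage. The authors also give up a comparative hypothesis that the design cannot address.

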Missing data will be categorized by cause (e.g., treatment discontinuation, withdrawal of consent, or loss to follow-up) and described in detail. For time-to-event analyses (e.g., Kaplan–Meier estimation), patients will be right-censored at the date of last contact if no event has occurred. Dropouts due to reasons unrelated to outcome (e.g., relocation or administrative issues) will be assumed non-informative.

For other outcome measures, complete-case analysis will be the primary analytic approach. In addition, we will perform sensitivity analyses using multiple imputation under the assumption of missing at random, where appropriate. This approach allows us to explore the robustness of our findings and assess potential bias due to missing data. The dropout rate and its potential effect on external validity will be reported and discussed as part of the study limitations.

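### Censoring at last contact treats every dropout as non-informative, although the plan claims this only for outcome-unrelated dropout, and no specified sensitivity analysis clearly probes it for the primary endpoints

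*Protocol article*

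**What the plan says.** Protocol article, section 2.8 (Data Analysis), sorts missing data by cause (treatment discontinuation, withdrawal of consent and loss to follow-up are the examples) and promises a description. For time-to-event analyses, "patients will be right-censored at the date of last contact if no event has occurred". The next sentence limits the accompanying assumption: "Dropouts due to reasons unrelated to outcome (e.g., relocation or administrative issues) will be assumed non-informative". Outcome-related dropout gets no rule of its own.

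The paragraph that follows deals with outcome measures other than the time-to-event ones. Complete-case analysis is primary there, and "we will perform sensitivity analyses using multiple imputation under the assumption of missing at random, where appropriate".

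Earlier in section 2.8, primary and secondary endpoints are given both as incidence proportions with exact 95% intervals and as Kaplan-Meier estimates. The primary analyses are also said to use Cox models.

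Section 2.4 (Study Size) lists an evaluation of patients with complete versus incomplete follow-up among the sensitivity analyses, without a method. It sets the target of 1000 and expects that "we estimate that most clinical endpoints will occur in 1% to 5% of patients". A dropout rate above 5% triggers further enrolment.

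Section 2.6 (Data Collection and Follow-Up) places final data collection at one year, or at 30 days after early discontinuation of rivaroxaban. For patients who stop one or both drugs, survival status is the only information it says is collected at one year. The footnote to Table 3 allows adverse-event recording to end 30 days after the last rivaroxaban dose.

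**The concern.** The plan recognises two kinds of dropout and states an assumption for one of them. It then applies to both a rule that is valid only under that assumption. Sorting by cause changes no estimate of a primary endpoint.

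Section 2.6 supplies a plausible informative group. A patient who stops rivaroxaban after a nuisance bleed may have a later infarction, stroke or revascularization that no stated procedure would capture.

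Events are expected to be few, so a handful of unseen ones among dropouts would move the reported rate, while the confidence interval reflects sampling error only. Under-counting would also lean towards the hypothesis in the Introduction that bleeding is not significantly increased, and would blur the contrast with COMPASS that the Discussion intends. Extra enrolment restores numbers but does not remove this bias.

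**Working it through.** **What each stated provision does for the primary endpoints**

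- *Censoring at last contact (2.8).* It applies to every event-free patient. Kaplan-Meier and Cox estimates under it are unbiased only if censoring is non-informative for all of them (for Cox, given the covariates).
- *Multiple imputation (2.8).* It sits in the paragraph on the remaining outcomes. It may be read to reach the incidence proportions, which are not time-to-event analyses. Either way it assumes missing at random, which is doubtful for outcome-related dropout.
- *Complete versus incomplete follow-up (2.4).* It is not restricted by outcome, so it can reach the primary endpoints. Comparing the groups uses only events seen before censoring.
- *Survival status at one year (2.6).* It helps with death but not with non-fatal components or bleeding. The text does not say whether this check counts as last contact.

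**Inputs**

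- n = 1000, and r = 1%, 3%, 5% (3% is a midpoint), from section 2.4.
- d = 50 unobserved patients (5% of 1000), from the enrolment trigger in section 2.4.
- Relative risk m in dropouts: my assumption, 5 and 10.

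There is no power calculation to reproduce. As a consistency check, 950 / (1 − 0.05) = 1000, so the target leaves 950 completers at 5% dropout. Expected events are 10 to 50 (1000 × 1% to 1000 × 5%), against 50 dropouts.

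**Simple illustration, dropouts unseen for the whole year**

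True rate = (950r + 50·m·r)/1000. Best case = 950r/1000. Worst case = (950r + 50)/1000. Example at r = 3%, m = 5: (28.5 + 7.5)/1000 = 3.6%.

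| Reported rate | Exact 95% CI, n = 1000 | m = 5 | m = 10 | Best case | Worst case |
|---|---|---|---|---|---|
| 1% | 0.48–1.83% | 1.20% | 1.45% | 0.95% | 5.95% |
| 3% | 2.03–4.26% | 3.60% | 4.35% | 2.85% | 7.85% |
| 5% | 3.73–6.54% | 6.00% | 7.25% | 4.75% | 9.75% |

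All 5-fold results lie inside the interval. The 10-fold results lie outside at 3% and 5%, and the worst case lies outside at all three rates.

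**Multiplying the hazard instead of the risk**

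With λ = −ln(1 − r) and hazard multiplier k after dropout:

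- all dropout at day 0: 0.95r + 0.05[1 − exp(−kλ)]
- dropout uniform over the year: 0.95r + 0.05{1 − [exp(−λ) − exp(−kλ)]/[(k − 1)λ]}

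| Reported rate | k = 5, day 0 | k = 5, uniform | k = 10, day 0 | k = 10, uniform |
|---|---|---|---|---|
| 1% | 1.20% | 1.10% | 1.43% | 1.22% |
| 3% | 3.56% | 3.28% | 4.16% | 3.61% |
| 5% | 5.88% | 5.46% | 6.76% | 5.95% |

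On this scale only one cell (5%, k = 10, day 0) leaves its interval.

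**If early discontinuers are also unobserved**

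The article gives no discontinuation rate. Assuming 10% to 20% of patients unobserved at 2 to 3 times the risk, a 3% rate becomes 0.90 × 3% + 0.10 × 6% = 3.3% at the low end and 0.80 × 3% + 0.20 × 9% = 4.2% at the high end.

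**The case against.** The strongest reply is that the article names its assumption, limits it sensibly, describes missingness by cause and promises to report dropout. How to probe outcome-related dropout is ordinary content for an analysis plan that is not shown, and the study is descriptive with no formal hypothesis test. This stands against any complaint that a method is merely absent. It does not answer the mismatch between rules that the article does state: the assumption covers one class of dropout and the censoring covers all.

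Three stronger readings are tempting, and the documents do not support them.

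- *That the primary endpoints go untested for dropout.* Section 2.4 plans the complete-versus-incomplete comparison, and imputation can be read to reach the incidence proportions. The comparison is weak, but it exists.
- *That dropout is expected to equal or exceed the primary event rates.* The 5% is a trigger for more enrolment, not a forecast. The 1% to 5% applies to most endpoints, and section 2.4 says the broader outcome definition "may lead to higher overall event rates". No rate is given for the composite.
- *That non-fatal events are definitely not recorded after discontinuation.* Section 2.6 mentions only survival status at one year; it does not exclude other data. Section 2.8 runs the study period to the end of the one-year follow-up and does not list stopping treatment as a reason to censor.

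It is also fair to say that the bias is modest under moderate assumptions. A 5-fold risk stays inside the interval. At a 5% rate, a 10-fold risk means half of all dropouts have an event within the year, and the worst case requires that every one does.

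**Conclusion.** The point holds as an inconsistency with a cheap remedy. The time-to-event analyses of both primary endpoints assume non-informative censoring for all dropouts, while the plan defends that assumption only for outcome-unrelated ones. No specified sensitivity analysis clearly tests the difference on those endpoints.

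With 5% unobserved, the likely shift is small: about 0.1 to 0.5 percentage points at a 5-fold hazard with dropout spread over the year, across rates of 1% to 5%. It exceeds sampling error only under a roughly 10-fold risk with early dropout, or near the worst case. These sizes rest on assumed multipliers and on 50 unobserved patients. They would grow if many patients stop rivaroxaban and their non-fatal follow-up does end early. The finding does not show that the reported rates will be wrong; it shows that readers could not judge how far dropout might move them. It is a cheap improvement, not a flaw that invalidates the plan.

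**What to change.** Keep censoring at last contact as the main analysis, and keep the planned imputation and follow-up comparison. Add, for both primary endpoints:

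1. Best-case and worst-case bounds.
2. A delta-adjusted analysis that imputes the remaining time to day 365 with the post-censoring hazard multiplied over a stated range, for example 1 to 10. Apply it to patients censored early for an outcome-related or unknown reason, including those whose non-fatal follow-up ended after discontinuation.
3. Ordinary censoring, unchanged, for relocation, administrative reasons and completion of the year.

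Also state which date counts as last contact when only survival status is known at one year, so that such patients are not counted as observed free of non-fatal events.

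The cost is a few sentences of analysis text and a little more programming, since causes of missing data are already to be categorised. The downside is a wider range shown beside the headline rate.
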